### Design

The trial will be a multicentre, open-label, cluster-randomised controlled trial, with two parallel groups (
Figure 1). Practices will be randomised to usual care (control), or a complex intervention comprising structured medication review involving both a pharmacist and a GP, supported by performance feedback, financial incentivisation, clinician training and clinical informatics (intervention). Patients with polypharmacy and potentially inappropriate prescribing will be recruited in each practice using a computerised search of health records. During the 26-week intervention delivery period, up to 50 patients in each intervention site will receive a medication review. Control practices will continue to provide usual care during this period. Every 4 weeks, over this 26-week period, a random sample of up to 10 consented patient participants in both intervention and control sites will be selected. An administrative eligibility check will be conducted to ensure the patient is still registered at the practice (if not, they will be excluded from the study). All eligible patient participants in intervention sites will then proceed to receive a medication review. Follow-up in both arms will then continue for 26 weeks after the eligibility check. Practices will continue to check eligibility for up to 10 patients every 4 weeks until they have confirmed a maximum of 50 eligible patient participants.

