### Usual care

Practices in the control arm will undertake their usual care for patients with polypharmacy. We anticipate this will comprise routine medication reviews, but no specific management strategy focused on polypharmacy. Control practices will be aware that the participant has consented to a trial of a polypharmacy intervention, but will not be aware of the specific aspect of potentially inappropriate prescribing that has led to the patient’s inclusion. Furthermore, changes to medications which trigger the review process are not mandated as part of the intervention. As such, the trial will not be withholding any clinical intervention targeted at the specific prescribing indicators which would otherwise have triggered a review. Control practices will not have access to the training programme, monthly feedback, computerised enhanced medication summary, or financial incentives. Some of the control practices may have access to a clinical pharmacist, whose role may include medication optimisation.

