### Safety reporting

Given the nature of participants in the IMPPP trial (older individuals with polypharmacy and therefore likely with multimorbidity), new diagnoses, hospital admissions and death are to be anticipated. An independent Data Monitoring Committee (DMC) will be established to assess trial safety and efficacy, consisting of three independent academic members including two statisticians and a clinician with relevant interests. Serious adverse events will be monitored, recorded and reported in accordance with the Good Clinical Practice (GCP) guidelines and the Sponsor’s Research Related Adverse Event Reporting Policy. Adverse events may be reported by participant or investigator, and assessment of intensity, relatedness and expectedness will be made by the Principal Investigator at each research site for all serious adverse events. Suspected unexpected serious adverse reactions (SUSARs) will be reported to the coordinating centre within 24 hours, and discussed at each scheduled DMC meeting. SUSARs will be additionally reported to the trial Sponsor within 5 days and the Research Ethics Committee within 24 days. As there is a potential for
*ad hoc* adverse events to be more readily identified in the intervention arm, the Principal Investigator at all research sites (irrespective of randomisation status) will undertake an additional proactive review of all participants’ hospital admissions, GP consultations and deaths during the study period and at the end of study follow-up. This will help identify differences in adverse event rates between study arms.

An adverse event will be deemed to have occurred where a change to the prescribed medication is required to counter a change in medication made at the initial intervention (patient-facing review) appointment. An adverse event will be considered expected if a) an adverse drug reaction (ADR) has occurred (i.e. consistent with the WHO definition of ADR, listed in the British National Formulary (BNF)
^
27

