^ as common or very common, and the drug or an interacting drug has been changed as a consequence of the IMPPP intervention), b) worsening of the drug clinical indication has occurred (i.e. where the indication is listed in the BNF, and the drug or an interacting drug has been changed as a consequence of the IMPPP intervention), or c) there is an adverse change in patient behaviour considered by the clinician to be consistent with that expected as a direct consequence of the intervention. Unexpected events will include ADRs considered uncommon, rare or unlisted in the BNF, or an intensity of event greater than that clinically expected, or a worsening of clinical condition despite a clinically appropriate drug change.

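### No control participant can meet the adverse-event definition, so the between-arm comparison of adverse-event rates intended under Safety reporting cannot be interpreted

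*Protocol article*

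**What the plan says.** All of the conflicting text stands in the Safety reporting section of the protocol article.

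The section first recognises that events may come to light more easily in the intervention arm. As a remedy, the investigator at every site ("irrespective of randomisation status) will undertake an additional proactive review") is to go through participants' admissions, consultations and deaths, both during the study and at the end of follow-up. The stated purpose is comparative: "This will help identify differences in adverse event rates between study arms".

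The next paragraph defines an event as a medication change that has to be made because of an earlier one, and it fixes where the earlier one took place. The condition is that the new change is "required to counter a change in medication made at the initial intervention (patient-facing review) appointment". The article gives no other adverse-event definition, and none for control participants.

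The rules for calling an event expected follow the same line. The first two require that "the drug or an interacting drug has been changed as a consequence of the IMPPP intervention", and the third requires a change in patient behaviour that follows directly from the intervention.

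On who has the review, the Design section says: "All eligible patient participants in intervention sites will then proceed to receive a medication review". The Usual care section says: "Practices in the control arm will undertake their usual care for patients with polypharmacy".

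**The concern.** The record review in both arms exists to correct for unequal detection. The definition undoes that correction, because it ties the event to an appointment that one arm never has. However carefully a control investigator searches the records, nothing found there can qualify.

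At stake is how a table of adverse-event rates by arm would be read. Any event at all in the intervention arm would appear as an excess over control, and that excess would say nothing about whether the intervention causes more or less harm than usual care. Control practices do change medicines. The Usual care section says: "We anticipate this will comprise routine medication reviews, but no specific management strategy focused on polypharmacy". The Statistical analysis section also allows that control practices may act to improve prescribing before the review point. A control patient whose medicine is changed at a routine review, and then changed again to counter a problem, has had the same kind of event but would not be counted.

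**Working it through.** The article states no adverse-event rate, so there is no figure to reproduce. The check is one of logic.

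**Step 1: conditions for an event.** From the definition under Safety reporting, a qualifying event needs (i) a medication change made at the intervention's patient-facing review, and (ii) a later medication change needed to counter it.

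**Step 2: who can satisfy condition (i).**

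| Group | Has the index appointment? | Can have a qualifying event? |
|---|---|---|
| Intervention, review attended | Yes (Design) | Yes |
| Intervention, review not attended | No | No |
| Control, routine review | No; a routine review is not the intervention appointment (Usual care) | No |
| Control, no review | No | No |

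**Step 3: what the comparison would estimate.** Let *a* be the proportion of intervention participants who have the review, *r* the probability of a qualifying event among them, and *h* the true probability in control of a medication change that has to be countered.

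- Recorded rate, intervention: *a* × *r*
- Recorded rate, control: 0 × *h* = 0
- Recorded difference: *a* × *r* − 0 = *a* × *r*

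*h* drops out. The recorded difference is the intervention arm's own rate. It is never negative, and it is the same whether control harm is lower, equal or higher. A rate ratio is undefined, because its denominator is zero.

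**Step 4: does other text widen the definition?** Expectedness rules a) to c) do not, since each depends on the intervention. The description of unexpected events does not name the intervention in its wording, but it sorts events that must already have met the definition. It does not create new ones.

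**Step 5: what lies outside the definition.** Serious adverse events are recorded and reported under Good Clinical Practice and the sponsor's policy, and nothing in the text limits that to one arm. Table 1 lists medication-related admissions and unplanned admissions from hospital records, and all-cause mortality from GP records. None of these refers to the review. The Statistical analysis section plans mixed models comparing secondary outcomes between arms. These comparisons are unaffected.

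**The case against.** The strongest reply is that the definition does not contain the word only. The preceding paragraph uses the term adverse event more broadly, since a worry that events are found more readily in one arm presupposes that they occur in the other. On this reading the definition adds a trial-specific, review-attributable event to ordinary serious-event reporting. Those serious-event definitions sit in the sponsor's policy and the full protocol, which are not shown.

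Part of this stands. The authors may well have intended it, and it is one of the two ways to reconcile the text. But the article does not say so. It states a comparison of adverse-event rates, then gives a single definition that one arm cannot meet, and does not say how that definition relates to serious-event reporting. That is a conflict between two statements, not detail left to a fuller document.

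Several stronger conclusions that a reader might draw are not supported:

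- **That the trial has no valid between-arm safety comparison, or that harm in control goes uncounted altogether.** Step 5 of the working shows otherwise.
- **That the data monitoring committee would be shown a biased table.** The article says that the committee assesses safety and discusses suspected unexpected serious adverse reactions. It does not say that the committee receives a between-arm table of the review-linked events.
- **That a false significant difference of some given size would follow.** The article states no test of adverse-event rates. Any count or test statistic would need an invented event rate and would have to borrow an intraclass correlation used to size the prescribing-indicator outcome. It would also have to treat every harm in the intervention arm as the result of a review change. The definition does not do that: harm there from ongoing prescribing, or from changes made outside the review, is not counted either.

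**Conclusion.** The point holds in a limited form. As written, the adverse-event definition makes the control count zero by construction, so a between-arm comparison of events so defined cannot be interpreted. Within that comparison the defect is complete, and it does not depend on any assumed rate or correlation. It rests on two readings, both taken directly from the text: that the stated definition is the one to be applied to the record review, and that a routine review in control is not the intervention appointment.

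It goes no further than that comparison. The primary outcome and its analysis are untouched. Medication-related admissions, unplanned admissions and mortality remain comparable between arms. So do serious adverse events, on the assumption that the sponsor's policy, which is not shown, defines them without reference to the review. The conflict should be resolved before any adverse-event rates are presented by arm.

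**What to change.** Reconcile the two statements under Safety reporting in one of two ways.

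(a) **Make the comparison arm-neutral.** For the between-arm comparison, define the event without reference to the trial review and count it from the eligibility check, which both arms undergo. Ascertain it by the record review already planned at all sites. Keep attribution to the IMPPP review as a causality field, summarised for the intervention arm only. The cost is wording in the protocol and safety forms, with no new data source. The downsides are more control events to classify and a causal judgement by investigators who know the allocation, which could itself differ between arms.

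(b) **Restrict the claim.** State that review-linked events are summarised for the intervention arm only and are not compared between arms, and that the between-arm safety comparison rests on serious adverse events, admissions and deaths. This costs a sentence or two and avoids the unblinded causal judgement in control. The price is that countered medication changes short of a serious event or an admission are then not compared between arms.

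Under either option, the text should also say how the trial-specific definition relates to serious adverse events reported under the sponsor's policy.

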### Ethics and governance

This study will be conducted in accordance with Good Clinical Practice guidelines, UK Policy Framework for Health and Social Care Research, and other relevant legislation (e.g. Data Protection Act 2018). The Sponsor is University of Bristol Research and Enterprise Development (reference 2018–2188). The sponsor and funder will have no role in the study design, writing of papers, or the decision to submit papers (including this protocol) for publication. Monitoring and auditing will be in accordance with the Sponsor’s policy. Protocol review has been undertaken by a NHS Research Ethics Committee (Wales REC 6, reference 19/WA/0090), and the study sponsor has reviewed the study procedures and ensured all indemnity and insurance requirements for the trial were in place prior to the start of recruitment. The current protocol version is 4.0. Protocol amendments will be approved by the REC and Sponsor. Participants will provide written informed consent, including options for participating in the process evaluation, and for sharing anonymous data for subsequent research.

Any medication optimisation strategy targeted at polypharmacy may result in a change (including reductions) in treatment; this is considered ethically acceptable assuming clinical decisions are made in agreement with the patient, are clinically justifiable, and are in the patient’s best interests. These conditions are met in the case of this trial since the study protocol does not pre-specify medication changes, which remain entirely at the discretion of clinicians and their patients.

In addition to the DMC described above, oversight of the trial will be undertaken by an independent Trial Steering Committee, chaired by a senior academic GP, including relevant methodological expertise, and clinical and patient representation, as well as representation from the trial team ([name]) as non-independent members.

The trial is registered with the ISRCTN registry (reference number ISRCTN90146150, registration date 28/03/2019).

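### The expected and unexpected rules in Safety reporting overlap without precedence, so a worsening of a changed drug's own indication can be classed either way

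*Protocol article*

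**What the plan says.** All the rules are in the Protocol article, Methods, Safety reporting.

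- **Expected, rule (b):** "b) worsening of the drug clinical indication has occurred". The bracket after it sets two conditions: the indication is one listed in the BNF, and "the drug or an interacting drug has been changed as a consequence of the IMPPP intervention".
- **Unexpected, next sentence:** the list includes ADRs that the BNF gives as uncommon or rare or does not list, then "or an intensity of event greater than that clinically expected", then "or a worsening of clinical condition despite a clinically appropriate drug change".
- **Who decides:** the Principal Investigator at each site judges intensity, relatedness and expectedness for every serious adverse event.
- **What follows from an unexpected call on a serious, suspected-related event:** "Suspected unexpected serious adverse reactions (SUSARs) will be reported to the coordinating centre within 24 hours, and discussed at each scheduled DMC meeting". The sponsor is told within 5 days and the Research Ethics Committee within 24 days.
- **What does not depend on expectedness:** serious adverse events are handled under GCP and the sponsor's reporting policy. The site investigator in both arms also actively reviews admissions, GP consultations and deaths.

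**The concern.** Expectedness separates a SUSAR from a related serious event that is not expedited. The two sentences should therefore give one answer for any given event, and for one recognisable kind of event they give opposite answers. Suppose a drug is appropriately changed at the review and the condition it was prescribed for then worsens. One site can cite rule (b) and record an expected event, while another can cite the closing clause and record an unexpected one. Both would be following the text.

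Two things are at stake. The first is whether such an event goes by the expedited route and is put to the DMC as a SUSAR. The second is whether SUSAR counts mean the same thing from one practice to the next. The Ethics and governance section acknowledges that the intervention may change or reduce treatment, so this kind of event can be foreseen.

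**Working it through.** No figure is involved, so the check sets the conditions of the two rules side by side and tests cases against them.

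| Condition | Rule (b): expected | Closing clause: unexpected |
|---|---|---|
| What worsens | The drug's indication, if listed in the BNF | A clinical condition, not further limited |
| What preceded it | The drug or an interacting drug was changed because of IMPPP | A drug change |
| Quality of the change | Not mentioned | Clinically appropriate |
| Direction of the change | Not mentioned | Not mentioned |
| Exclusion of the other rule | None | None |

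Each case below is taken already to count as an adverse event under the article's definition, meaning that a further prescribing change was needed to counter one made at the review.

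1. **Appropriate change because of IMPPP, and the BNF-listed indication worsens.** Every condition of rule (b) is met. Every condition of the closing clause is also met, because an indication is a clinical condition. The event is both expected and unexpected.
2. **Change judged not appropriate, and the indication worsens.** Only rule (b) applies, so there is no conflict.
3. **Appropriate change, and a condition worsens that is not the indication of the changed drug or of one it interacts with.** Only the closing clause applies, so there is no conflict.

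The conflict is confined to case 1. Two narrower readings might remove it.

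- *The closing clause is about unusually severe worsening.* Severity already has its own clause, "or an intensity of event greater than that clinically expected", so the closing clause must cover something else.
- *The word despite limits the clause to changes that should have helped the condition.* Rule (b) asks only that the drug was changed, in whatever direction. A change meant to help the indication, followed by its worsening, still meets rule (b). The overlap becomes smaller but does not vanish.

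Consequence of each call for a serious, suspected-related event in case 1:

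| Site's call | Route stated in the article |
|---|---|
| Expected, rule (b) | Serious adverse event handling under GCP and sponsor policy; no expedited timeline stated |
| Unexpected, closing clause | SUSAR: coordinating centre 24 hours, sponsor 5 days, REC 24 days, discussion at scheduled DMC meetings |

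**The case against.** The best defence is that the two sentences were meant for different situations. Rule (b) would cover worsening caused by the change, and the closing clause worsening that occurred although the change should have helped or been harmless. The terms also differ: one rule speaks of a drug's indication, the other of a clinical condition. That may well be the intention, but the text does not state it. A site investigator has only the words, and these allow both classes. The defence makes the overlap smaller and shows how easily it could be closed, but it does not close it.

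A reader might also infer more than the document supports.

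- *That the overlap is almost total.* This would rest on the Ethics and governance section, where changes in treatment are acceptable "assuming clinical decisions are made in agreement with the patient, are clinically justifiable" and the article adds "These conditions are met in the case of this trial". That is a general ethical premise for leaving medication decisions to clinicians and patients. It is not a test applied to each change for safety classification, and the article does not equate clinically justifiable with clinically appropriate. The extent of the overlap cannot be derived from it.
- *That the DMC sees nothing but SUSARs, or that events classed as expected escape any check.* The DMC's stated remit is trial safety and efficacy. Serious adverse events are reported whatever their expectedness, under a sponsor policy that is not shown, and sites in both arms carry out the proactive review. Table 1 also takes unplanned and medication-related admissions from hospital data and deaths from GP records, none of which depends on the expectedness call.
- *That site-level judgement of expectedness is itself an error.* It is a stated choice. Any central confirmation may sit in documents that a condensed article does not reproduce.

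**Conclusion.** The inconsistency is real and limited. A worsening of the changed drug's BNF-listed indication after a clinically appropriate, IMPPP-related change meets both rules, and the article does not say which prevails. For the subset that is serious and suspected to be related, SUSAR status turns on which sentence the site applies, so SUSAR counts may not be comparable across practices. The effect is on expedited reporting, the stated DMC discussion of SUSARs and consistency of classification. Loss of events does not follow.

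The size cannot be given, because the article states no rate for such events. The planned intervention arm is about 37 × 50 / 2 = 925 participants if the arms are equal and recruitment is full. That is the number who could have a trial-driven change, not the number affected.

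The conclusion assumes that the closing clause carries its ordinary meaning, with a drug's indication counted as a clinical condition. If the full protocol or site guidance already confines one of the two rules, the conflict lies only in the article's wording. The point should be corrected, but it does not threaten the trial's main comparison.

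**What to change.** Reconcile the two sentences so that each event has one class. State whether worsening of the changed drug's own indication belongs under rule (b) or under the closing clause, and limit the other accordingly. Which class is right is for the trial team to decide. Issue the settled wording to every site as guidance, so that all Principal Investigators apply the same rule.

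The contradiction calls for nothing more. Routing all related serious events by the 24-hour path, or confirming expectedness centrally, would redesign safety reporting, which this point does not require.

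The cost is a wording amendment, which under Ethics and governance needs REC and sponsor approval, plus a short note to sites. According to Current trial status, participant recruitment began on 24/1/2022 and follow-up was expected to run to July 2023. Events already classified may therefore need to be re-checked against the settled rule, and any whose class changes handled accordingly.
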